## Results

This study was funded by the Craig H. Neilsen Foundation in April 2017 (Multimedia Appendix 1). It was approved by the institutional review boards at Virginia Commonwealth University and the Hunter Holmes McGuire Veterans Affairs Medical Center that same year. Participant recruitment and data collection began in 2018. As of March 2021, 31 caregiver-patient dyads (n=62) had enrolled in the study. Data analysis will begin toward the end of the grant cycle in March 2022, with results expected to be published in May 2022.

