## Methods

### Study Design

This study is a prospective, mixed-method, randomized controlled trial incorporating a before-and-after design with a standard-of-care control wherein caregivers receive no formalized, structured postdischarge support. The study is recruiting over a period of 48 months.

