### Participants, Recruitment, and Sample Size

The eligibility criteria for individuals with SCI and caregivers are the following: (1) between the ages of 18 and 89 years; (2) able to verbally communicate in English; (3) access to a computer, telephone, or other device capable of telecommunication; (4) no other serious mental or neurological disorders; (5) no active serious substance use disorder; and (6) being a dyad composed of 1 individual with a new diagnosis of SCI or significant new loss of function related to an old SCI and 1 individual identifying as a new informal caregiver. All individuals with SCI are those participating in a comprehensive residential rehabilitation program.

A power analysis was performed using G*Power 3.1. An estimated medium effect size of Cohen *f*=.25 was used to determine the sample size needed for a repeated-measures multivariate analysis of variance (RMANOVA) with 3 time points and 2 groups. With 80% power (1 - β), a sample size of 44 dyads is needed in order to detect the hypothesized medium-sized effects on the various outcomes. We selected a 48-month enrollment period because, based on SCI admissions data and previous studies conducted at the 2 rehabilitation sites, this window is necessary to enroll 44 patient-caregiver dyads (n=88), of which 22 dyads will be in the treatment group and 22 will be in the control group. This RMANOVA would uncover all large and medium-sized effects, but no small-sized effects.

Recruitment is conducted on site and in-person by either the research coordinator or the site’s principal investigator (PI). Patient-caregiver dyads are randomly assigned to the TAP treatment or control group, and each individual with SCI and caregiver is paid US $20 per data collection for a total of US $60 each.

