### Data Collection

#### Data Collection 1

After enrollment and immediately before discharge (as well as before Session 1 for the TAP group), demographic and baseline data are collected from the individual with SCI and caregiver separately by a study coordinator. A study coordinator reads items aloud from an assessment packet (unless a participant explicitly requests a paper-and-pencil format) to the individual with SCI and caregiver, noting participants’ responses. The caregiver packet includes validated measures of caregivers’ quality of informal care provided, depression, relationship satisfaction, burden, caregiving self-efficacy, health status, and positive affect/well-being. The packet for the individual with SCI includes validated measures of functional status, perceptions of quality of informal care received, depression, relationship satisfaction, self-perceived burden, health status, and positive affect/well-being. In rare cases, after Data Collection 1 has been conducted, where the patient’s discharge is moved to a later date, data collection may be readministered to ensure data accuracy.

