### Data Analysis

A Greenhouse-Geisser–adjusted RMANOVA with 1 fixed effect of treatment condition (TAP vs control), the repeated measures over time (baseline and 2 and 4 months after discharge), and the treatment condition by time interaction will be conducted for the set of dependent variables. If an omnibus effect is found, follow-up Holm-Bonferroni–corrected ANOVAs will identify specific locations of effects. Our research has shown that these dependent variables rarely correlate with each other higher than .60 in SCI caregivers [5] so do not reach the .70 level that is often identified as problematic in RMANOVA [33].

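### The dates do not fit the design: a 2018 start, 48 months of enrollment and a 4-month outcome run past the March 2022 analysis, when about 37 to 42 dyads rather than 44 would be complete at the documented pace

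*Protocol article*

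**What the plan says.** All statements are in the protocol article.

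- **Enrollment window** (Study Design): "The study is recruiting over a period of 48 months". Participants, Recruitment, and Sample Size ties the window to the target: "this window is necessary to enroll 44 patient-caregiver dyads (n=88".
- **Start** (Results): "Participant recruitment and data collection began in 2018". The month is not given.
- **Accrual** (Results): "As of March 2021, 31 caregiver-patient dyads (n=62) had enrolled in the study".
- **Outcome times** (Data Analysis): the model uses "the repeated measures over time (baseline and 2 and 4 months after discharge". Data Collection places baseline "After enrollment and immediately before discharge (as well as before Session 1 for the TAP group", so a dyad's 4-month visit falls at least 4 months after its enrollment.
- **Number needed** (Participants, Recruitment, and Sample Size): "a sample size of 44 dyads is needed in order to detect the hypothesized medium-sized effects on the various outcomes", at 80% power.
- **Analysis date** (Results): "Data analysis will begin toward the end of the grant cycle in March 2022, with results expected to be published in May 2022".

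The article does not say that enrollment will close early, that the window has been shortened, or that the March 2022 analysis will use fewer than 44 dyads.

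**The concern.** The planned model needs three time points per dyad, and the sample size is stated for that model. If the full window is needed to reach 44, the last dyads enroll near its end, and their third time point is due 4 months or more after that. An analysis dated March 2022 sits before that point for every possible 2018 start.

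The number needed and the number to be enrolled are both 44, so the article states no slack to absorb the loss. At stake is whether the three-time-point comparison rests on the number of dyads that the plan itself calls necessary, and whether the reader is told if it does not.

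**Working it through.** **1. The plan's own figure of 44.** The article gives Cohen f = 0.25, m = 3 time points, k = 2 groups and 80% power. It does not give alpha, the correlation among repeated measures (rho) or the sphericity factor (epsilon). For the group-by-time interaction, the noncentrality is lambda = f² × N × m × epsilon / (1 − rho), with degrees of freedom (k − 1)(m − 1) × epsilon and (N − k)(m − 1) × epsilon.

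- Assuming alpha 0.05, rho 0.2 and epsilon 1, N = 44 gives lambda = 0.0625 × 44 × 3 / 0.8 = 10.3 and power 0.813. This is the smallest even N that reaches 0.80.
- Rho 0.5 with epsilon 0.5 also leads to 44 (power 0.801).
- Rho 0.5 with epsilon 1 would need only 28.

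So 44 can be reproduced, but only with inputs that the article does not state.

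**2. Calendar from the window.** Last 4-month visit = start + 48 months + at least 4 months.

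- Start 1 January 2018: window closes about 31 December 2021, last visit about 30 April 2022. This is 1 to 2 months after analysis begins.
- Start 1 February 2018: last visit about 31 May 2022. Any later start takes it past the publication month.
- Start 31 December 2018: window closes about end December 2022, last visit about end April 2023. This is 13 to 14 months after analysis begins.

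**3. Complete dyads in March 2022.** A dyad with 4-month data in March 2022 must have enrolled by 1 to 30 November 2021, even if it was discharged on the day of enrollment. Assuming constant accrual:

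rate = 31 / (months from start to the March 2021 count); complete = 31 + rate × (months from that count to the November 2021 limit).

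| Start | Count taken | Rate per month | Enrolled by | Complete |
|---|---|---|---|---|
| 1 Jan 2018 | 31 Mar 2021 | 31/39 = 0.795 | 1 Nov 2021 | 31 + 7 × 0.795 = 36.6 |
| 1 Jan 2018 | 31 Mar 2021 | 31/39 = 0.795 | 30 Nov 2021 | 31 + 8 × 0.795 = 37.4 |
| 31 Dec 2018 | 31 Mar 2021 | 31/27 = 1.148 | 30 Nov 2021 | 31 + 8 × 1.148 = 40.2 |
| 31 Dec 2018 | 1 Mar 2021 | 31/26 = 1.192 | 30 Nov 2021 | 31 + 9 × 1.192 = 41.7 |

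The range is about 37 to 42, which is 2 to 7 below 44. At the planned pace of 44/48 = 0.917 per month, counted from the start, the figure runs from 34 × 0.917 = 31.2 (start 31 December 2018, limit 1 November 2021) to 47 × 0.917 = 43.1 (start 1 January 2018, limit 30 November 2021). This is also below 44.

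**4. When the 44th dyad would be complete.** The remaining 44 − 31 = 13 dyads take 13/1.192 = 10.9 months from 1 March 2021 at the fastest pace, which is about end January 2022. At the slowest pace they take 13/0.795 = 16.4 months from 31 March 2021, which is about mid-August 2022. Adding 4 months puts the 44th dyad's last visit between about end May and mid-December 2022.

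**5. Pace needed to meet the date.** Thirteen dyads in 7 to 9 months is 13/9 = 1.44 to 13/7 = 1.86 per month. Against the matching observed rates this is 1.44/1.192 = 1.2 to 1.86/0.795 = 2.3 times faster.

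**6. Cost.** Standard errors scale as √(44/n): √(44/42) = 1.02 and √(44/37) = 1.09. In the rho 0.2, epsilon 1 variant of step 1, power is 0.793 at 42 and 0.735 at 37, against 0.813 at 44. With rho 0.5 and epsilon 1 it would still be 0.914 at 37.

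**The case against.** The strongest reply is that the sentence is an administrative forecast, placed beside the funding and approval dates. It dates the start of analysis work. It names no data cut-off, lock or between-arm comparison, and the Data Analysis section requires 4-month data without naming a date. Preparatory work in March while the last visits come in would be consistent with the text. With a start in January 2018 the last visit would fall by about the end of May 2022. Lock and trigger rules may also stand in a full plan that is not shown.

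Much of this stands, and it rules out three stronger readings that a reader might infer:

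- **That 44 complete dyads are impossible.** This follows only under constant accrual. The article gives one count and no start month, and its remark that the window is necessary is a planning projection. Thirteen dyads by November 2021 is unlikely but possible.
- **That the arms will be compared while follow-up is open.** The article does not say so.
- **That leaving out late-enrolled dyads biases the comparison.** A calendar cut-off applies to both randomized arms alike. What the documents support is a loss of precision.

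The misfit of the dates remains. The article states the start year, the window, the outcome time and the analysis date itself, so the conflict does not arise from condensation. The preparatory-work reading also leaves little or no time before May 2022 for a January 2018 start, and fails for any start after about 1 February 2018.

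**Conclusion.** The point holds as a conflict among the article's own figures. For every 2018 start, the stated window plus the 4-month outcome ends between about end April 2022 and end April 2023, after the stated start of analysis. That result assumes nothing about accrual.

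The expected size of the shortfall, about 37 to 42 complete dyads instead of 44, rests on constant accrual, an unknown start month taken over all of 2018, discharge immediately after enrollment, and no dropout. Relaxing either of the last two lowers the number. The loss is modest: standard errors about 2 to 9% larger. Whether power drops below 80% depends on a correlation and sphericity factor that the article does not give. As dated, though, the calendar is not expected to deliver the number of three-time-point dyads that the plan says 80% power needs, and the article does not say so.

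**What to change.** Reconcile Study Design, Participants, Recruitment, and Sample Size, Data Analysis, and Results. Define the start of the between-arm analysis by an event: completion of the last enrolled dyad's 4-month data collection. Move the March and May 2022 dates to follow from it.

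If the end of the grant cannot move, state that enrollment closes at least 4 months before the analysis, with an allowance for the time from enrollment to discharge. Then restate the expected number of complete dyads and the power it supports. Give that number as a projection with its assumptions (start month, accrual rate, dropout), not as an established figure.

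The cost is a delay of some months, or a slightly less favourable stated sample size. No extra participants, staff or procedures are needed.

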## Discussion

One primary goal of this study is to actively affect the care of individuals with SCI and their informal caregivers at a systematic level. As such, the caregiver guidebook developed for this study will be made freely available online so that any clinician may give it to any new, informal caregivers as they adjust to their new role. If the results are significant, the research team will make the intervention and results available through manuscripts and conference presentations. Detailed descriptions of the intervention will be published, and training videos will be made available online.

This study’s use of PhD psychology students as the study’s interventionists allows for a role that could create a future pipeline and documentation for training rehabilitation psychology students using the TAP system. Students could also receive course credit for practicum work in SCI rehabilitation settings while simultaneously gaining experience in telepsychology and with underserved populations. The use of PhD psychology students as interventionists helps defray health care costs and reduces the burden placed on the medical center’s staff [34].

The TAP intervention, especially if used as a training program for PhD students, could be implemented for minimal or even negligible health care costs. These savings could be passed to the individual with SCI and his or her informal caregiver. We also anticipate that participants will find the telepsychology intervention to be both more convenient and less of a strain on their resources than traditional, in-person sessions.

Given the study’s presence at both a VA medical center and an urban academic medical center, any study findings should have high generalizability to both the general population and veterans with SCI. Our TAP for SCI caregivers is innovative in that it fills one of the biggest gaps in SCI rehabilitation by aiming to improve the mental health of and quality of informal care provided by caregivers immediately as they transition into their caregiving role. The study’s telehealth format surmounts geographical barriers and links SCI caregivers via telehealth technology to the specialized center from which the individual with SCI received acute rehabilitation, thereby overcoming the discontinuity in care that all too often affects individuals with SCI and their family after discharge. If shown in the proposed study to improve caregiver mental health, informal care, and SCI rehabilitation, the TAP for SCI caregivers could be exported and evaluated much more widely across other rehabilitation facilities in the United States and hopefully become part of the standard of care for SCI.

## Appendix

Multimedia Appendix 1 Peer-review report by Craig H Neilsen Foundation.

## Abbreviations

CESD-R: Center for Epidemiologic Studies Depression Scale-Revised
HRQoL: health-related quality of life
PI: principal investigator
RMANOVA: repeated-measures multivariate analysis of variance
SCI: spinal cord injury
SF-12: 12-item Short Form
TAP: Transition Assistance Program
VA: Veterans Affairs
